## Abstract

**Background:**

Allergic rhinitis (AR) is a noninfectious chronic inflammatory disease of the nasal mucosa characterized mainly by itching, sneezing, nasal congestion, and rhinorrhea. It is mediated by immunoglobulin E (IgE). AR is one of the most common allergic diseases globally, affecting 10% to 20% of the population worldwide, with some regions even reaching rates as high as 50%, posing a global health issue. The prevalence of AR has been increasing since the 1960s, with a significant increase in recent years. At present, modern medicine—including desensitization therapy, the use of antiallergic drugs, antihistamines, hormones, and other treatments—can improve symptoms or regulate the immune system. However, both short- and long-term efficacy remain limited, as symptoms often recur after treatment cessation, and long-term drug use is associated with toxicity and side effects.

**Objective:**

Acupoint catgut embedding (ACE) therapy is widely used to treat AR in China. ACE therapy has been reported to be effective in managing the symptoms of AR, but the evidence faces methodological limitations. Therefore, we designed a parallel-arm, randomized controlled, multicentered, placebo-controlled, and single-blinded trial to evaluate the efficacy and safety of ACE therapy for AR.

**Methods:**

This study will be a parallel-group, patient-blind, placebo-controlled randomized controlled trial conducted in the Third Affiliated Hospital of Sun Yat-sen University, Ningxia Chinese Medicine Research Center, and the Affiliated Hospital of Shanxi University of Traditional Chinese Medicine. The trial consists of a 4-week treatment period, along with a 3-month follow-up. After providing written informed consent, eligible participants will be randomized at a ratio of 1: 1 into one of 2 groups: the ACE group receiving treatment and the sham ACE group. Both groups will receive conventional loratadine treatment.

**Results:**

The funding began in January 2022. The study was initiated on February 1, 2025, and will end in February 2026. Patient recruitment has already started, and the study results will be released in March 2026.

**Conclusions:**

We expect that this research will provide important insights into the efficacy of ACE treatment for AR and generate robust data for the foundation of future research in this field.

**Trial Registration:**

Chinese Clinical Trial Registry ChiCTR2500095634; https://www.chictr.org.cn/historyversionpubEN.html?regno=ChiCTR2500095634

**International Registered Report Identifier (IRRID):**

PRR1-10.2196/63933

## Introduction

Allergic rhinitis (AR) is a noninfectious chronic inflammatory disease of the nasal mucosa characterized mainly by itching, sneezing, nasal congestion, and rhinorrhea. AR is mediated by immunoglobulin E (IgE). It is one of the most common allergic diseases, affecting between 10% and 20% of the population worldwide [1], with some regions even reaching rates as high as 50%, posing a global health issue. The prevalence of AR has been increasing since the 1960s [2], with a significant increase in recent years [3]. At present, modern medicine—including desensitization therapy, antiallergic drugs, antihistamines, and hormones—helps improve symptoms and regulate the immune system. However, the short- and long-term efficacy is limited, as symptoms often recur after treatment cessation, and long-term drug use is associated with toxicity and side effects [4]. Allergen-specific immunotherapy (AIT) is the only means of altering the natural immunological course of allergic diseases and achieving long-term remission. Pharmacological measures can suppress the immune response and ameliorate symptoms, but there is a risk of relapse soon after stopping these measures [5]. Currently, the main drugs for treating AR are H1 antihistamines, nasal steroid hormones, and leukotriene receptor antagonists. The control and safety of nasal symptoms have been verified; however, limitations remain in preventing the recurrence of AR [6]. Catgut implantation at the acupoints is a subtype of acupuncture, in which a catgut is embedded in the acupoint using a special needle. The catgut is absorbed by the tissue over a period of time. Therapeutic effects can be achieved by continuing stimulation caused by the catgut at the acupoint. Therefore, catgut implantation at the acupoint may be effective in treating some chronic diseases such as AR. Although acupoint catgut embedding (ACE) therapy has been used to treat diseases for thousands of years in China, there have been very few clinical trials strictly designed to verify the efficacy and safety of this treatment for AR [7]. It is necessary to obtain stronger evidence for catgut implantation at the acupoints for treating AR. Research on ACE therapy for AR primarily focuses on regulating cytokines, influencing neurotransmitters, and inhibiting immune molecules such as IgE. At the cytokine regulation level, acupoint embedding research concentrates on interventions targeting inflammatory factors and transforming factors. Inflammatory factors include interleukin-17(IL-17), interleukin-4 (IL-4), and interferon-gamma (IFN-γ), and transforming growth factors include transforming growth factor β1, among others [8-12]. ACE therapy intervenes in neurotransmitters mainly by participating in the release of various immunologically active substances, such as substance P. Research has found that embedding therapy can alleviate rhinitis-related symptoms by regulating substance P and nitric oxide levels [13-15]. The process begins with mechanical stimulation, followed by biological and chemical stimulation. The gradual softening, decomposition, liquefaction, and absorption of the catgut thread within the acupoint provides prolonged stimulation, reducing the likelihood of recurrence. Therefore, the treatment interval can be extended to once every 10 days, greatly improving patient compliance. Moreover, catgut thread, as an allogeneic protein stimulus, can better regulate the relative balance of the body's internal environment, enhance immune function and stress resistance, and reduce allergic reactions. Therefore, it is considered an excellent method for treating AR [16].

A recently published systematic review confirmed the effect of ACE therapy. However, it also pointed out that previous randomized controlled trials (RCTs) faced a variety of methodological limitations, including the absence of sample size calculation, inappropriate control groups, and multicenter RCTs and blind designs [17]. Therefore, it is necessary to conduct large-scale and rigorously designed RCTs to overcome the identified methodological issues. The primary objective of this study is to evaluate the efficacy of ACE therapy for AR, with a focus on reducing recurrence. Secondary objectives include assessing whether ACE therapy can (1) improve patients' quality of life and (2) change the dosage of the relief medication (RM).

## Methods

### Study Design

This study will be a parallel-group, patient-blind, placebo-controlled RCT conducted in the Third Affiliated Hospital of Sun Yat-sen University, Ningxia Chinese Medicine Research Center, and the future Affiliated Hospital of Shanxi University of Traditional Chinese Medicine. The flowchart of this trial is shown in Figure 1. The trial consists of a 4-week treatment conducted along with a 3-month follow-up. After providing written informed consent, eligible participants will be randomized at a ratio of 1: 1 into one of 2 groups: an ACE group receiving ACE treatment or a sham ACE group receiving sham ACE treatments. Both groups will receive conventional loratadine treatment.

**Figure 1 figure1:**
[figure not shown]
Trial flow diagram. ACE: acupoint catgut embedding; AE: adverse event; BRE: blood routine examination; FU: follow-up; RCAT: Rhinitis Control Assessment Test; RM: relief medication; TNSS: Total Nasal Symptom Score; TOSS: Total Ocular Symptom Score.

### Patient Information

Participants will be recruited via advertisements, posters, leaflets about the trial, and doctor referrals from otorhinolaryngology clinics in the 3 study hospitals. Interested individuals will need to contact research assistants by phone or email. Trial information and consent forms will be sent to them to read before scheduling their first visit. In the first visit, screening evaluations will be conducted and recorded to ensure eligibility. For each participant who is eligible and willing to participate in the trial, research assistants will provide a signed consent form. The inclusion criteria for this trial are: (1) age between 18 and 65 years old; (2) meeting the diagnostic criteria for perennial AR; and (3) currently experiencing symptomatic attacks, able to accurately describe their condition, and willing to provide informed consent and participate in the clinical study.

Patients with AR were diagnosed based on the following criteria: (1) the presence of 2 or more symptoms including sneezing, clear watery nasal discharge, itchy nose, or nasal congestion that persists or occurs for more than 1 hour per day; (2) ocular symptoms such as itchy, watery, or red eyes; (3) nasal endoscopy showing pallor and edema of the nasal mucosa; and (4) a positive seasonal allergen test result for serum-specific IgE [18]. The exclusion criteria included: (1) recent respiratory infection or acute paranasal sinusitis within the past 14 days; (2) evidence of inflammation on chest X-ray; (3) history of chronic paranasal sinusitis or current diagnosis via X-ray examination; (4) the presence of organic lesions in the nasal cavity or recent nasal surgery; (5) diagnosis of paroxysmal respiratory diseases such as asthma; (6) recent use of H1-antihistamines, steroids, decongestants, or other medications affecting the respiratory system within the past 14 days; (7) specific immunotherapy or systemic hormone therapy within the last year; (8) recent use of acupuncture, moxibustion, cupping, nasal inhalation of traditional Chinese medicine, or other traditional therapies within the past 14 days; and (9) determination by clinical investigators that the patient is unable to adhere to the treatment regimen.

### Randomization and Allocation Concealment

A block randomization sequence was generated by SAS software (version 9.2; SAS Institute Inc), which was performed by Guangdong Provincial Hospital of Chinese Medicine’s Key Unit of Methodology in Clinical Research. Eligible participants will be randomly assigned to either the ACE group or the sham ACE group at a ratio of 1:1. An independent researcher will prepare treatment cards, on which a serial number and one of 2 names are printed, each representing one of the 2 groups. This independent researcher will be responsible for selecting and adding intestinal thread to the injection needles according to the respective groups. Treatment allocations will be stored in password-protected files and held independently by staff of the Key Unit of Methodology in Clinical Research. While receiving the first treatment, the participants will be given sequential treatment cards from independent researchers to ensure adequate concealment. The participants will be allocated into one of 2 groups according to the name printed on their treatment card.

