### Intervention

To ensure operational consistency, all patients will receive unified treatment set by the same doctor. The research assistant will add intestinal threads to the injection needles according to the respective groups. The ACE group will undergo ACE. The bilateral YingXiang (LI20), QuChi (LI11), JianJing(GB21), YinTang(GV24+), and DanZhong (CV17) points will be disinfected. Detailed positioning data are shown in Table 1 and Figure 2. The patient will assume a supine position, and acupoints will be located, marked with a marker, and disinfected with iodophor cotton swabs.

**Table 1 table1:** Location of acupoints from the World Health Organization (WHO) 2014 Standard Acupuncture Point Locations in the Western Pacific Region (SPAR) study.

Acupoint	Location
YingXiang (LI20)	On the face, next to the midpoint of the outer edge of the alar, in the nasolabial groove
QuChi (LI11)	On the lateral aspect of the elbow, at the midpoint of the line connecting LU5 with the lateral epicondyle of the humerus
DanZhon (CV17)	In the anterior thoracic region, at the same level as the fourth intercostal space, on the anterior median line
JianJing (GB21)	In the posterior region of the neck, at the midpoint of the line connecting the spinous process of the seventh cervical vertebra (C7) with the lateral end of the acromion
YinTang (EX-HN3)	At the midpoint of the line connecting the 2 medial ends of the eyebrows

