**Figure 2 figure2:**
[figure not shown]
Diagram of the prescribed acupoints from the World Health Organization (WHO) 2014 Standard Acupuncture Point Locations in the Western Pacific Region (SPAR) study.

The practitioner will wear aseptic gloves, cut the absorbable surgical suture around 5 mm, and place it into the front end of the needle tube. The structure of the acupuncture needle is illustrated in Figure 3. The doctor’s left thumb and index finger will tighten the skin around the operation site, and the needle will be inserted vertically with a catgut-burying needle in their right hand at a depth of 0.5 cm. The needle will be slightly lifted to stimulate the acupoints, and after getting qi, the left hand will push the needle core inward while the right hand withdraws the needle tube outward, embedding the surgical suture in the acupoint. After the stitches are placed, the pinhole will be pressed with aseptic gauze for a while and covered with a bandage or infusion paste.

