### Ethical Considerations

This study protocol has been approved by the Ethics Committee of the Guangzhou University of Chinese Medicine (B2014-014-01). It is explicitly outlined to all participants that the trial involves a waiting-list group and that informed consent to participate includes an agreement to undergo 3 months of clinical monitoring. All participants are provided with enough time to decide whether to sign the informed consent. This clinical study will adhere to the ethical principles outlined in the Declaration of Helsinki (2024) and relevant national regulations. Prior to study initiation, the trial protocol underwent rigorous review and approval by the Ethics Committee of Ningxia Medical University (2024-075). Written informed consent must be obtained from each participant before randomization.

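### The ethics section tells participants of a waiting-list group that the two-arm sham design does not contain, and the text conflicts on who loads the thread, which puts participant blinding at risk

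*Protocol article*

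**What the plan says.** **Arms.** The Study Design section sets up two groups: "an ACE group receiving ACE treatment or a sham ACE group receiving sham ACE treatments". The randomization section repeats this: "Eligible participants will be randomly assigned to either the ACE group or the sham ACE group at a ratio of 1:1". The Abstract gives the same two arms, and both receive loratadine.

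**What participants are told.** Ethical Considerations says it is made explicit to everyone that "the trial involves a waiting-list group".

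**Who loads the thread.** There are three statements:
- Randomization and Allocation Concealment, of the person who prepares the treatment cards: "This independent researcher will be responsible for selecting and adding intestinal thread to the injection needles according to the respective groups".
- Intervention, opening paragraph: "The research assistant will add intestinal threads to the injection needles according to the respective groups".
- Intervention, text after Figure 2, where the practitioner is to put on gloves and then "cut the absorbable surgical suture around 5 mm, and place it into the front end of the needle tube".

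**Cards.** Each card carries a serial number and one of two names that stand for the groups. It is handed to the participant at the first treatment, and "The participants will be allocated into one of 2 groups according to the name printed on their treatment card".

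**Blinding.** Participants and outcome assessors are to be blinded, and the statistician is to be unaware of the group assignments. Researchers and acupuncturists know the allocation.

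**The concern.** The primary outcome is recurrence within 3 months of stopping medication. The Outcome Measurement section ties it to the RCAT, which participants score themselves every week. TNSS is self-assessed and TOSS is a questionnaire that participants complete. Blinded outcome assessors add little protection when the participant supplies the score, so the comparison depends on participants not knowing their arm.

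Two statements bear directly on that. A participant led to expect a waiting-list comparator could reasonably take being needled as a sign of active treatment. And if the thread is cut and loaded at the couch in one arm only, the two procedures can look different to the person undergoing them. The waiting-list sentence is also a matter of consent in its own right, because recruitment is already under way.

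**Working it through.** There is no figure in the plan to reproduce. The check sets the statements side by side.

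**1. Arms in the design against arms in the consent statement.**

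| Place | Arms described | Waiting list? |
|---|---|---|
| Abstract, Methods | ACE, sham ACE | No |
| Study Design | ACE, sham ACE | No |
| Randomization and Allocation Concealment | ACE, sham ACE, 1:1 | No |
| Intervention | ACE, sham ACE | No |
| Ethical Considerations | mentions a waiting-list group | Yes |

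Four descriptions agree and one does not. Under 1:1 allocation to two named arms there is no place for a third group. Sham participants are needled weekly from the start, so the sham arm cannot be called a waiting list either.

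**2. Who loads the thread.** Three role names appear: independent researcher, research assistant, practitioner. The first two could be one person under two titles. The practitioner cannot be reconciled in that way, because the practitioner performs the insertion.

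**3. Whether the choice of role matters to the participant.** The Intervention section has the ACE participant lie supine and the points marked and disinfected. The practitioner then cuts and loads the suture and inserts the needle. The sham sequence goes from positioning, marking, disinfection and gloving straight to insertion, and says that no suture is put in the tube. It contains no dummy cutting or loading. Followed literally, the ACE arm has a step that the sham arm lacks. Five acupoints are named and there are four weekly sessions. If each point receives its own thread at each session (an assumption), the step occurs at least 5 × 4 = 20 times per ACE participant and 0 times per sham participant. If needles arrive already prepared, as the randomization section suggests, the difference disappears.

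**4. Separation from recruitment.** Under Patient Information, "research assistants will provide a signed consent form", and research assistants also take enquiries. If the research assistant who loads by group is one of these people, recruiting staff learn past allocations from a blocked sequence. The text does not say whether it is the same person.

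**5. Cards.** With two names used throughout, one participant who learns their arm reveals the arm of everyone holding the same name. A serial number alone would not do this, and the allocation list is already held in protected files by the methodology unit.

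**The case against.** The best defence is that much of this may be loose wording. The waiting-list sentence may be a leftover that never reached the consent form. The independent researcher and the research assistant may be the same person. The names on the cards may be neutral codes, since the text presents the cards as a means of concealment. Unblinded staff are disclosed openly, and the Discussion names single-blinding as the main limitation.

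Much of this stands, and it rules out several stronger readings that a reader might infer:

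- *The cards print the arm in clear.* The text says only that a name represents a group. A code fits that wording, so this is a risk left open and not a contradiction.
- *Recruiting staff can predict the next allocation, with a calculable success rate.* Block size is not stated, nothing says that the person who consents also loads, and an external party administers the block randomization. No prediction figure can be attached to this trial.
- *All 126 planned participants have been wrongly consented.* The consent form is not available, the number enrolled so far is not given, and the sentence does not say that the sham is undisclosed.
- *The blinding questionnaire is worthless.* It asks participants whether they believe they received ACE, which suggests they may know of an inactive alternative. The documents do not settle the matter.

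The defence does not remove two things. The ethics sentence is false for this design whether or not the form repeats it. And the practitioner loading step conflicts with the other two statements and has no counterpart in the sham.

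**Conclusion.** Two points hold on the text alone. The waiting-list statement contradicts the two-arm sham-controlled design. The loading statements contradict one another, and the practitioner version makes the two procedures differ in a way that participants could notice. The cards are an avoidable risk and a lesser point.

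The effect cannot be quantified from the documents. It depends on whether the consent form carries the waiting-list wording, where loading takes place in practice, and whether the card names are fixed for the whole trial. The importance comes from the outcome: self-rated scores leave participant blinding as the main safeguard. The changes should be made, and the consent form should be checked promptly because enrolment has begun.

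**What to change.** 1. Rewrite the sentence in Ethical Considerations so that it describes the ACE versus sham ACE comparison. Check the consent form against it. Only if the form has the same error, notify the ethics committee and inform or re-consent those already enrolled.
2. Reconcile the three loading statements. Give preparation of the needle in both arms, loaded or empty, to the independent researcher named in the randomization section. It should be done out of the participant's sight, by someone who does not recruit or take consent. Move the cutting and loading step out of the practitioner's sequence, but keep the stated suture length in the text, since it appears nowhere else.
3. Print only the serial number on the card the participant receives, and leave the link to the group with the independent researcher.

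The cost is modest: edits to a few sentences, needles prepared before each session by a role the plan already has, reprinted cards and, if the form is wrong, an ethics notification with contact to enrolled participants. Arms, outcomes, sample size and analysis are untouched.

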### Blinding

The researchers will assign intervention measures to the participants according to their allocated groups. The participants will be blinded to their group allocations in this single-blind study, whereas the researchers and acupuncturists will be aware of the group allocations. To minimize bias, outcome assessors will be blinded throughout the study.

A first-level blind base will be established for data statistics, ensuring the statistician is unaware of the group assignments. All operations will be performed in accordance with established standard operation procedures. After each treatment session, the participants in the ACE and sham ACE groups will complete a questionnaire on whether they believe they received ACE treatment and how certain they are that active treatment was received on a 0-to-10 numeric rating scale, where 10 represents absolute certainty [18]. Both the block randomization and the blinding questionnaire will be exclusively administered by a single external party.

